#### Data collection plan

At enrollment, in the intervention arm, we will collect the following data from the TB treatment card: sex, age, type of TB, smear status, and bacillary load and drug susceptibility test results of the index case. In addition, we will collect age, sex, and kinship to the index case of the child contact. We will also interview the caretaker, to collect the sex, age, occupation, and TB history of the caretaker (if she/he is not the index case), and household socio-economic status and sleeping arrangements of the child and the index case. At the middle and end of the study period, we will review treatment cards to collect data on the main outcome (the dates of IPT pick up) from the back of the TB treatment cards. In the control arm, we will review the TB treatment card to collect index case and child contact characteristics and dates of IPT pick up from the back of the TB treatment cards where it is registered. This will be done at the middle and the end of the study period. A participant timeline is presented in Fig. 1.

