### Study participants

Eligible participants will be caretakers of children who are (1) < 5 years old, (2) a contact of a TB patient, and (3) have an isoniazid preventive treatment (IPT) prescription from the TB physician. We will exclude caretakers not interested in participating in the study, those who do not have a mobile phone or, since August 2020, a smartphone with internet access using WhatsApp.

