### Study procedures

#### Recruitment

TB nurses will ask eligible participants if they are interested in participating, and those who accept will be approached by the research nurse, who will inform caretakers about the study; those who provide written consent will be enrolled.

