#### Randomization

We will randomize 30 clusters — health facilities — 10 to the intervention and 20 to control. We aim to recruit 10 children from different households in each cluster. Twelve of the 48 health facilities were excluded from these classifications as they had less than 1 TB case notification per month. To randomize the 36 health facilities, we classified them into 11 groups: 10 groups of 3 health facilities and one group of six facilities based on the number of TB cases reported in 2018, and the number of children < 5 started on IPT in 2018 as registered in routine health information systems. The group with 6 health facilities had the smallest number of cases per year. To select 2 control facilities and 1 intervention facility, we randomly selected from the group with the highest burden (group 1) until reaching the 10 intervention and 20 control facilities. Only the group classification and not the name of the facility was visible during randomization. Random numbers were generated with the Excel formula Rand() next to each group for the 36 health facilities. A witness set the criteria to the assignment of health facilities from groups 1 to 10. After we completed the assignments, the names of the health facilities were unblinded and the list of intervention and control facilities was made public (Available at bit.ly/3FRTA01). There were three stand-by health facilities for both groups in case a replacement was needed.

Based on 2018 TB case notifications, in which each facility reported an average of 68 TB patients (index cases) per year, and each case has a mean of four household contacts, of which, on average one is < 5 years old and that ~ 10% of children would be non-eligible for IPT (Multidrug-resistant TB contact, contraindications to isoniazid, other) and that 30% of those eligible for IPT would not be started on it (as per our findings), we estimated that more than 150 children would be eligible for the study in 1 year.

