### Data management and analysis

Data will be imported into Stata V16. We will compare the proportion of children who completed IPT in both groups with statistical tests for small groups in an intention-to-treat approach, including all enrolled participants in the denominators. We will also compare the median number of weekly IPT pick-ups. We will compare the characteristics of caretakers, index cases, and children of the intervention and control arm. Missing data will be reported in descriptive tables. Medians and interquartile ranges will be calculated for continuous variables and proportions for categorical variables. Despite randomization, there may be confounding present regarding the probability of completing IPT. Potential confounders include the index case characteristics (sex, age, smear status), child characteristics (sex, age, kinship to the index case), caretaker’s characteristics (sex, age, kinship to the child, and to the index case, occupation, and education) the socio-economic status of the family and the health facility. To determine an unconfounded estimate of the effect of the intervention in the proportion of children who completed IPT, we will test models with a multivariate backward regression analysis. A saturated model with variables associated with IPT completion in our preliminary findings (smear status and treatment outcome of the index case, kinship and TST result of the child [14] and other variables associated (*p* < 0.1) with the outcome in the bivariate analysis will be tested against a model with variables with the weakest associations eliminated one by one. We will analyze the timing of the drop-outs (caretakers not coming back to pick up IPT) with Cox regression and the factors associated to that timing with a multivariate Cox regression analysis. We will report the proportion of enrolled to those eligible overall for the intervention group as well as per health facility, and we will report the full cascade of IPT (evaluation, prescription, initiation, completion) for the intervention and control facilities during the study period. As the data for the outcomes are routinely collected, we will follow the REporting of Studies Conducted using the Observational Routinely Collected Health Data (RECORD) statement to report the study findings [37].

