### Limitations and alternative approaches

Contamination may occur if caretakers of different arms share the booklet. Although this is possible, we will recruit participants from a large geographical area of 700,000 population to reduce the clustering of caretakers who know each other. This will be explored with caretakers at the end of the intervention. We will conceal group allocation but cannot blind the intervention to those delivering it or receiving it.

Considering the non-monetary nature of the incentive, we do not expect adverse effects of incentives such as fraudulent practices or the perverse incentive effect in which the incentive provokes the opposite of the intended behavior.

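### The plan does not settle how control children are identified; on its natural reading, consenting phone owners are compared with any child on a treatment card

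*Protocol article*

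**What the plan says.** All references are to the Protocol article.

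- **Study participants** sets the exclusions without naming an arm: "We will exclude caretakers not interested in participating in the study, those who do not have a mobile phone or, since August 2020, a smartphone". The smartphone must have WhatsApp.
- **Recruitment** likewise names no arm: "those who provide written consent will be enrolled". **Power calculations** speaks of enrolling 100 children in intervention clusters and 200 in control clusters.
- **Data collection plan** separates the arms. For the intervention arm it describes data taken at enrolment and an interview covering caretaker characteristics and household socio-economic status. For controls the only source described is the card: "In the control arm, we will review the TB treatment card to collect index case and child contact characteristics", together with pick-up dates, reviewed at the middle and the end of the study period.
- **Standard of care** lists what the card holds on contacts: sex, age, kinship, tests, IPT prescriptions and pick-ups.
- **Data management and analysis** defines intention-to-treat as all enrolled participants. It adds "We will report the proportion of enrolled to those eligible overall for the intervention group", with no control counterpart, and also "we will report the full cascade of IPT (evaluation, prescription, initiation, completion) for the intervention and control facilities during the study period".
- **Randomization** says that after assignment "the list of intervention and control facilities was made public". **Limitations and alternative approaches** says "We will conceal group allocation but cannot blind the intervention to those delivering it or receiving it".

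**The concern.** In a cluster trial, randomising facilities protects the comparison only if children enter it by the same route in both arms. Here the intervention arm is filtered by interest, consent and phone or smartphone access. The card records none of these, so card review alone cannot apply the same filter to controls. Control characteristics and outcomes also come from one document, read when pick-up dates are already on it. An analysis of all enrolled participants inherits whatever difference this creates.

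The planned adjustment does not help. Data management and analysis lists caretaker education, occupation and family socio-economic status among the potential confounders and plans to compare caretakers between arms. Yet the caretaker interview is described only for the intervention arm. What is at stake is whether the primary comparison is like with like.

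**Working it through.** **1. The two readings side by side.**

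| Reading | Supported by | Consequence |
|---|---|---|
| Controls come from cards only | Data collection plan; enrolled-to-eligible for the intervention group only | Different populations; selection possible with the outcome visible |
| Controls are screened and consented alike | Study participants, Recruitment and Power calculations name no arm | Same filter, but recruiters can know the arm from the public list |

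Both cannot be the plan, and each leaves a problem.

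**2. The plan's own sample size.** Inputs: 30% v 70%, ICC 0.38, 8 per cluster, 1:2 allocation, 80% power. Two-sided alpha of 0.05 is my assumption. With continuity correction, 21 + 42 children are needed under individual randomisation. The design effect is 1 + 7 × 0.38 = 3.66. Then 21 × 3.66 = 76.9 and 42 × 3.66 = 153.7, which is 10 + 20 clusters of 8, or 240 children. The figure reproduces. It has no bearing on selection, but its ICC is used in step 4.

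**3. Spurious difference under card-only controls.** Assume no intervention effect and 30% completion among all children on the cards. Let f be the share of caretakers who have a phone and consent, and let p and q be completion among enrollable and other children, linked by an odds ratio OR. The document gives neither f nor OR; both are assumptions.

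f·p + (1 − f)·q = 0.30, so the spurious difference is p − 0.30 = (1 − f)(p − q).

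Example, f = 0.7 and OR = 2: p = 0.341, q = 0.205; difference = 0.3 × 0.136 = 0.041.

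| f | OR 1.5 | OR 2 | OR 3 |
|---|---|---|---|
| 0.9 | +0.8 | +1.3 | +1.8 |
| 0.7 | +2.5 | +4.1 | +6.1 |
| 0.5 | +4.2 | +7.2 | +11.1 |

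(percentage points; with OR = 1 the difference is zero)

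**4. Chance of a false positive.** At 10 per cluster the design effect is 1 + 9 × 0.38 = 4.42, so the effective sizes are 100/4.42 = 22.6 and 200/4.42 = 45.2. A two-sided 5% unpooled z-test rejects in 5.1% to 14.6% of trials over this grid. At an assumed ICC of 0.05 the upper end is 34.7%.

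**5. Size of the pool.** The inputs in Randomization give 68 × 1 × 0.9 × 0.7 = 42.8 eligible children per facility-year, or about 1,285 over 30 facilities. The same paragraph concludes only that more than 150 would be eligible in a year. That is about 5 per facility over 30 facilities, or 15 if it refers to the 10 intervention facilities. The room for choosing 10 controls per facility is therefore unknown.

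**6. Dilution of an all-starters analysis.** The effect shrinks to the design difference times the share of starters enrolled. With 42.8 starters and 10 enrolled, the share is 10/42.8 = 23%, and 40 points become about 9. With 15 starters the share is 67%, and 40 points become about 27. A window longer than a year lowers the share further.

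**The case against.** The strongest reply is that the article never says control caretakers are not approached, do not consent or are exempt from the phone criterion. Read literally, eligibility, consent and enrolment apply to both arms. The Data collection plan says where data come from, not necessarily how children are found, and a condensed article may leave the sampling rule to the full protocol. This stands in part: card-only recruitment is an inference, though the natural one from two sections. What remains is a conflict within the article about how its arms are formed.

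A reader might infer more than the document supports:

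- **That controls will be picked by outcome.** No section describes this. The plan leaves it possible, and the pool may be small (step 5).
- **That intervention children are all enrolled in person.** After the restart, enrolment is by phone following a brief in-person introduction.
- **That the bias must favour the intervention.** Early drop-outs may be missed in the intervention arm yet appear on control cards. But Study participants requires only a prescription, so an enrolled child who never starts would count against the intervention.
- **That the concealment statement is false.** Randomization does describe hiding facility names until assignment was complete, and Limitations admits that delivery cannot be blinded. Concealment of assignment is real; it does not extend to choosing participants.

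It is also fair that the full cascade, already planned for both arms, covers all starters. As described, it is a report and not a comparison set against the enrolled result.

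**Conclusion.** The point holds as an unresolved conflict with a conditional bias. If controls come from cards alone, the arms are different populations, and the null difference is zero only if enrollability is unrelated to completion. Under the stated assumptions the distortion is about +1 to +11 points. That is well below the 40-point design difference, but a larger sample does not remove it and it would matter for a modest observed effect. More extreme inputs give more: half enrolled and completion of 45% v 15% gives 0.5 × 30 = +15 points. Nothing in the document supports that case in particular. Covariates on the card may absorb a little of the bias, but the caretaker and socio-economic variables most likely to drive selection are not described for controls. If controls are consented alike, the populations match on paper, but recruitment with the allocation known remains a risk that the article does not acknowledge.

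**What to change.** 1. State one identification rule for both arms, and reconcile Study participants, Recruitment, Data collection plan, Power calculations and Data management and analysis with it. If controls come from cards, take consecutive IPT starters, one per household, in the same calendar window as intervention enrolment, listed without sight of later pick-up dates. Count follow-up from the same start point in both arms. This needs saying, because the Abstract refers to children who initiated IPT and Study participants to children with a prescription.
2. Report enrolled-to-eligible in both arms.
3. Pre-specify a facility-level sensitivity analysis of all under-5 IPT starters on the cards of the 30 facilities, regardless of consent or phone, using the cascade data already planned.
4. Limit the concealment sentence to facility assignment, and say that allocation was known when participants were recruited.

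The cost is wording and extra card abstraction, with no new recruitment. The all-starters effect is diluted by children who were not enrolled, possibly heavily. It serves as a check on selection beside the enrolled comparison and does not replace it.

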**Fig. 1 Fig1:**
[figure not shown]
Participant timeline

#### Power calculations

We expect to increase IPT completion from 30 to 70% with the intervention. A structured behavioral intervention that included self-monitoring and incentives to increase adherence to IPT among children increased IPT completion (OR 2.4, 95% CI 1.7–3.5) [36]. Our intervention will use incentives targeting children and two additional tools targeting the caretaker. Therefore, we expect to increase it by 3.5, the upper CI. In that scenario, the outcome would occur in 70% of the intervention arm. Considering an intra-cluster correlation coefficient of 0.38, we will need to recruit 8 children in each of the 30 clusters (10 intervention, 20 control), to be able to detect that difference with 80% power. Considering potential losses (e.g., children whose IPT is stopped for medical reasons), we will recruit 10 children per cluster. Therefore, we will enroll 100 children in the intervention clusters and 200 children in the control clusters. Sample size calculations were made in Stata v.12 (Stata Corp, 12.0, College Station, TX).

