## Background

Children exposed to tuberculosis (TB) are at high risk for developing severe and fatal forms of TB, such as TB meningitis, which has a low probability of survival, and a high risk of neurological sequela [1, 2]. In 2020, an estimated 1 million children had TB (11% of the global burden) and 204,000 died (16% of the global burden) [3]. In a recent meta-analysis, the case-fatality ratio for children less than 5 years old was 43.6% [4], compared to 3.0% in adults [5].

To prevent TB in children we need to diagnose and treat adult TB, the main infectious source [6], vaccinate newborns with BCG to decrease the incidence of severe forms of pediatric TB [7], and provide tuberculosis preventive therapy (TPT) to children with latent TB infection (LTBI); the latter reduces TB risk by more than 60% [8–10]. Isoniazid preventive therapy (IPT) is the most widely implemented TPT in high and moderate incidence countries. Other effective regimens such as 3 months of weekly rifapentine plus isoniazid, a 3-month regimen of daily isoniazid plus rifampicin, or 4 months of daily rifampin, are not widely implemented yet. In 2020, 36 countries reported use of rifapentine-containing regimens for research purposes and in some specific populations [9]. IPT delivery faces challenges through the continuum of care, from ruling out active TB to maintaining adherence to a daily dose of isoniazid for 6 months [11]. In 2019, only 29% of household contacts aged less than 5 years received TPT and the number of people initiating TPT dropped from 3.6 to 2.8 million between 2019 and 2020, due to the COVID-19 pandemic [5]. TPT completion rates are not reported by TB programs. However, a systematic review found that approximately 20% of children starting TPT completed it, even in high-income countries[12]. In Peru, a review of national routine surveillance data found that only 22% of eligible children < 5 years old received a full course of IPT between 2015 and 2016 [13], which is consistent with studies in Lima [14, 15].

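### The 70% completion target does not follow from the odds ratio cited for it: an odds ratio of 3.5 on 30% gives 60%, for which the planned design has about 64–67% power (two-sided 0.05 assumed)

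*Protocol article*

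**What the plan says.** All of this is in the Power calculations section of the protocol article. It opens with the target: "We expect to increase IPT completion from 30 to 70% with the intervention". The support offered is a behavioural intervention in children that "increased IPT completion (OR 2.4, 95% CI 1.7–3.5"). Because this trial adds tools aimed at the caretaker, the authors adopt the top of that interval and draw the consequence: "Therefore, we expect to increase it by 3.5, the upper CI. In that scenario, the outcome would occur in 70% of the intervention arm".

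The sample size follows. "Considering an intra-cluster correlation coefficient of 0.38", the article says, "we will need to recruit 8 children in each of the 30 clusters (10 intervention, 20 control"), for 80% power to detect that difference. Ten children per cluster are to be recruited to allow for losses, which makes 100 and 200 children. The section does not state alpha, sidedness or the test behind the calculation.

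**The concern.** The 70% is presented as the result of applying 3.5 to the baseline, and 3.5 is a limit of an odds ratio. Odds ratios act on odds, and the step from 30% to 70% is larger than 3.5 on that scale. A reader is therefore told that the trial has 80% power for an effect at the edge of published evidence, when the effect it is powered for lies beyond that edge.

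What is at stake is how the result is read. If the true effect is as large as the most favourable value in the cited interval, the trial still has a sizeable chance of missing it. A non-significant result could then be taken as evidence against an effect that the design was not well placed to detect.

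**Working it through.** **Inputs.** From Power calculations: control completion 30%; target 70%; odds ratio 2.4 (1.7 to 3.5), with 3.5 adopted; intra-cluster correlation 0.38; 10 intervention and 20 control clusters; 8 children per cluster (10 recruited); power 80%. Assumed: two-sided alpha 0.05, equal cluster sizes and an unadjusted comparison of two proportions.

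**Step 1: the derivation of 70%.**
- Odds at 30%: 0.30/0.70 = 0.4286. Times 3.5 = 1.5. Proportion = 1.5/2.5 = 60%.
- Odds ratio for 30% to 70%: (0.70/0.30)/(0.30/0.70) = 5.44.
- Odds ratio 2.4 on 30%: 0.4286 × 2.4 = 1.0286; 1.0286/2.0286 = 50.7%.
- Read as a risk ratio: 3.5 × 30% = 105%, which is impossible.

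**Step 2: effective sample size.**
- Design effect at 8 per cluster: 1 + 7 × 0.38 = 3.66.
- Effective n: 80/3.66 = 21.9 (intervention) and 160/3.66 = 43.7 (control).

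**Step 3: the plan's own figure, 30% versus 70%.**
- With continuity correction, 21 and 42 effective children are needed for 80% power. Solving 10m/(1 + 0.38(m − 1)) = 21 gives m = 21 × 0.62/(10 − 21 × 0.38) = 6.4, so 7 per cluster, close to the stated 8.
- Power at 8 per cluster: 82.3% (pooled variance, continuity-corrected), 88.7% (pooled), 89.5% (t, 28 df), 91.5% (unpooled).
- The stated 80% for 30% versus 70% is therefore met.

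**Step 4: the same design for 30% versus 60%.**
- SE = √(0.24/21.9 + 0.21/43.7) = 0.1256. z = 0.30/0.1256 = 2.39. Unpooled power = Φ(2.39 − 1.96) = 66.6%.

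| Method, two-sided 0.05 | 8 per cluster | 10 per cluster | Unlimited children per cluster |
|---|---|---|---|
| Unpooled normal | 66.6% | 68.1% | 74.5% |
| Pooled normal | 65.0% | 66.5% | 73.2% |
| t, 28 df | 63.5% | 65.0% | 71.5% |
| Pooled, continuity-corrected | 54.5% | 56.3% | 64.4% |

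A beta-binomial simulation with a t-test on cluster proportions gave 63.6% at 8 per cluster and 65.2% at 10.

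**Step 5: why there is a ceiling.** As the number of children per cluster grows, effective n in the intervention arm tends to 10/0.38 = 26.3. For 80% power against 60% it must be (1.96 + 0.84)² × (0.24 + 0.21/2)/0.30² ≈ 30.1 by the unpooled formula, or 31 by the pooled one. Both exceed 26.3.

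**Step 6: the point estimate.** For 30% versus 50.7% at 8 per cluster, power is 36.9% (unpooled), 37.5% (pooled), 34.8% (t) and 27.8% (continuity-corrected).

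**Step 7: what is detectable with 80% power at 8 per cluster.** 30% versus about 65% (unpooled), about 66% (pooled or t) or about 69% (continuity-corrected). These are odds ratios of about 4.3, 4.5 and 5.2.

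**Sensitivity to sidedness.** At one-sided 0.05 without correction, power for 60% is 76–77% at 8 per cluster, with a limit of 82–84%; by the pooled formula it passes 80% at about 21 per cluster. With correction, the one-sided limit is 75.5%.

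**The case against.** The strongest reply is that the sample size is sound for the difference it names. The section opens with 30% to 70% and claims 80% power for that difference, and the recomputation gives at least that. This stands. A reader might infer that the 80% figure is itself wrong, and the article does not support that reading. The fault is in the sentence that derives 70%.

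A second reply concerns the ceiling. A reader might conclude that no number of children per cluster could ever give 80% power for 60%. That depends on two-sided testing, which the article does not state, and fails at one-sided 0.05 without correction. Two-sided fits better: one-sided 0.05 would put power for 70% at about 90–95% at 8 per cluster, further from the stated 80%. The limit also assumes an unadjusted comparison. Randomization within facility groups and the planned regression model could reduce the between-facility variance that counts, by an amount the article does not allow one to quantify.

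Third, the replacement figures depend on the method, and the continuity-corrected one comes closest to the plan's 8 per cluster. This too stands, so ranges are given.

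It is also tempting to explain the 70% as 3.5 times a 20% baseline. That is a guess: an odds ratio of 3.5 on 40% gives 70% as well, and the article does not show how the figure was reached.

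Finally, the Background reports 72% completion with a multi-component intervention in Lima. That study was non-randomized, included adults and is not used in the power section, but it makes 70% arguable as a direct assumption. It does not rescue the derivation as written.

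**Conclusion.** The derivation is wrong as written. An odds ratio of 3.5 on 30% is 60%, and the 70% target is an odds ratio of 5.44, beyond the upper limit cited for it. This part rests on no assumption outside the paragraph.

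The power consequence is conditional on two-sided 0.05, equal cluster sizes and an unadjusted comparison. Under those conditions, even the most favourable value in the cited interval leaves the trial 13 to 16 points short of 80% power at 8 per cluster without continuity correction, and about 25 points short with it. More children per cluster would not close the gap: the limit is 72–75%, or 64% corrected. Unequal cluster sizes would lower power further.

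**What to change.** Rewrite the paragraph in Power calculations as follows.

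- Say that an odds ratio of 3.5 on 30% completion gives 60%.
- State alpha, sidedness and the calculation method, including whether a continuity correction was used.
- Report the resulting power for 30% versus 60% and for the cited point estimate of 2.4 (30% versus 51%).
- Give the difference detectable with 80% power by the stated method: 30% versus about 65–66%, or about 69% with continuity correction (two-sided 0.05).
- If 70% is kept as the target, present it as a direct assumption equal to an odds ratio of 5.4, and delete the statement that it follows from the cited upper limit.

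The cost is a restated planning figure. It requires no added children or clusters.
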